#### *Treatment of missing data*

Missing data will be imputed for the primary outcome measure for any patients are missing one or more components required to calculate VFDs. Fully conditional specification will be used for imputation; the imputation model will include randomised treatment arm, study site and the two study strata variables. Ten sets of imputed data will be created using the methods described for the primary outcome. A pooled common effect estimate and 95% confidence interval will be generated from the imputed datasets.

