### ***Withdrawal of Participants***

The investigator may withdraw a patient from the study treatment and follow-up procedures if the patient:

- Is in violation of the protocol;
- Experiences a serious or intolerable adverse event
- Develops, during the course of the study, symptoms or conditions listed in the exclusion criteria
- Requires early discontinuation for any reason

The investigator will also withdraw all participants from the study treatment if the study is terminated. Patients are free to withdraw from the study at any time upon their request or the request of their legally acceptable representative. Withdrawing from the study will not affect their access to standard treatment or their relationship with the hospital and affiliated health care professionals

When a participant is withdrawn from the treatment and/or the study by the investigator, the reasons for withdrawal shall be recorded and captured in the CRF by the site research assistant. Where the participant withdraws from the treatment and/or the study themselves or is withdrawn by their parent/guardian, the site research assistant shall attempt to ascertain the reason(s) for withdrawal from the parent/legal guardian or competent participant and, where provided, record this data. Any results obtained prior to withdrawal from the treatment and/or the study will be included in the analysis, unless the participant or their parent/guardian withdraws consent to use any of the participant's data.

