## **Outcome measures**

The definition and detail of calculation of outcome measures can be found in the Supplementary Appendix (Section S2), alongside the Stata scripts written to calculate these outcomes (available on GitHub (16)). Briefly, the outcomes are:

- Primary outcome measure: VFDs within 28 days from start of CPB
- Secondary outcome measures:

- Individual VFD components (i.e. duration of mechanical ventilation, death within 28 days after CPB start)
- Individual and components of composite measure of LCOS, and/or ECLS within 48 hours after CPB start and/or death within 28 days after CPB start;
- Length of PICU stay after CPB start;
- Length of hospital stay after CPB start;
- Process of care measures:
  - Treatment with ECLS within 48 hours after CPB start;
  - Duration of postoperative time spent with open chest including unplanned chest reopening after CPB start;
  - Treatment and duration of treatment using inhalational nitric oxide postoperatively after CPB start;
  - Treatment and duration of treatment of postoperative renal replacement therapy (includes peritoneal and continuous venous-venous haemodialysis) after CPB start;
- Physiological descriptors:
  - Postoperative troponin levels during the first 24 hours postoperatively;
  - Severity and duration of postoperative organ dysfunction; and
  - Postoperative acute kidney injury (AKI) and serum creatinine levels measured during the first 24 hours.

For the purposes of analysis and reporting, LCOS within 48 hours after CPB start, ECLS within 48 hours after CPB start, death within 28 days after CPB start and length of stay in PICU and hospital are classified as potentially patient-important secondary outcomes. The remaining secondary outcomes will be reported to describe patient physiology and processes of care only.

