## **Statistical analysis**

### *Statistical analysis principles*

- Analyses will be conducted based on the intention-to-treat principle. Specifically, patients who are eligible, who do not meet any exclusion criteria and who undergo randomisation will be analysed based on the treatment group they were allocated to, independent of the compliance with the treatment delivered.
- Participants who had more than one surgery before their second birthday will only have data related to their first surgery for which study consent was available analysed.
- Statistical tests will be two-sided applying a statistical significance level of 0.05. As we are not correcting for multiplicity when comparing secondary or other outcomes, such results will be considered exploratory and will be reported as point estimates with 95% confidence intervals (CIs).
- If there is missing data for the primary outcome measure for any participants, imputation methods will be used.
- Continuous variables will be assessed for normality; this will be undertaken using visual inspection of histograms and Q-Q plots.
- Standard descriptive statistics will be used when summarising variables; frequencies (percentages) for discrete variables, mean and standard deviation (SD) for continuous

variables, or, if continuous variables are non-normally distributed, median with interquartile range (IQR).

- This analysis plan and the primary manuscript will only include analyses up to 28 days. We will present analyses of postoperative delirium, health care costs, inflammatory markers and long-term outcomes (12 months and later post procedure) separately.
- Pre-planned subgroup analyses will be performed including the pre-defined study strata; these will be executed regardless of any potential treatment effect on the primary or secondary outcomes in the main cohort.
- To ensure transparency and reproducibility, the Stata code that will be used to analyse the final study data is available on GitHub (16).
- The trial statistician will be blinded to the treatment group until the analyses outlined in this SAP have been completed.
- Changes in the analysis plan by the investigators effective after publication of this SAP will be declared as such.

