### 404 *Primary Outcome*

405 The primary outcome of VFD will be calculated as the sum of all episodes of invasive respiratory support, which require an endotracheal tube in situ,  
406 from start of CPB and censored at 28 days after CPB start. Patients who die within this time period will be assigned a value of zero for the VFD outcome.  
407 Ventilated days do not include non-invasive ventilation or high-flow nasal cannulae. Patients who receive a tracheostomy will be counted as ventilated  
408 as long as they receive positive pressure ventilation through the tracheostomy. The individual components of VFDs (duration of invasive respiratory  
409 support from start of CPB within the first 28 days, and death within the first 28 days) will also be presented.

410

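### The model that imputes ventilator-free days ignores ventilation and vital status already observed, so some imputed values can contradict the record and some precision is lost

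*Combined protocol and SAP*

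**What the plan says.** The SAP's statistical analysis principles give the general rule: "If there is missing data for the primary outcome measure for any participants, imputation methods will be used". The section Treatment of missing data sets the trigger: "Missing data will be imputed for the primary outcome measure for any patients are missing one or more components required to calculate VFDs". It names fully conditional specification as the method and says "the imputation model will include randomised treatment arm, study site and the two study strata variables". It adds: "Ten sets of imputed data will be created using the methods described for the primary outcome".

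The outcome is given under Outcome measures as "Primary outcome measure: VFDs within 28 days from start of CPB", and its parts as "Individual VFD components (i.e. duration of mechanical ventilation, death within 28 days after CPB start". Supplementary Appendix S2 adds the rule for deaths: "Patients who die within this time period will be assigned a value of zero for the VFD outcome".

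Partial records are foreseen. Under Withdrawal of Participants the protocol states "Any results obtained prior to withdrawal from the treatment and/or the study will be included in the analysis", unless consent to use the data is withdrawn. The SAP section Datasets analysed likewise keeps data up to withdrawal where this is permitted. Protocol section 7.2 notes that, after transfer to another facility, access to records depends on parental permission.

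The missing-data section does not say whether VFD itself or its components are imputed. It sets no limits on the imputed values and gives no role to ventilation or status observed before follow-up stopped.

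**The concern.** Most of the information about an incomplete VFD lies in the child's own record up to the last observation. A child extubated on day 2 and followed to day 20 has a nearly settled outcome. A child still intubated on day 14 has a hard ceiling on it. A model with only arm, site, age stratum and physiology treats the two alike if they share those four values, and draws for each from the spread of the whole group.

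There are two consequences. Individual imputed values can be ones the record rules out. And information the trial has collected, and intends to keep, does not help estimate the primary outcome, so the treatment comparison is less precise than it could be.

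**Working it through.** **Where the 10% comes from.** The SAP's sample size uses 0.2 SD, 90% power and two-sided 5%: n per arm = 2 × (1.960 + 1.2816)² / 0.2² = 525.4. Adding 15% and 10% gives 525.4 × 1.15 × 1.10 = 664.6 (1,330 in total), or 525.4 × 1.25 = 656.7 (1,314 in total). The stated 1,320 is reproduced. The 10% is a planning allowance for withdrawals; the documents give no rate of partial VFD records.

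**Logical limits.** I take VFD as 28 minus ventilated days in survivors and 0 in deaths. S2 literally describes summing the ventilated episodes, so the subtraction is my reading.

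- Intubated throughout and withdrawn on day 14: VFD is at most 28 − 14 = 14.
- Extubated on day 2 and withdrawn on day 20: VFD is at most 28 − 2 = 26. If the child survives but is re-intubated, it is at least 26 − 8 = 18. If the child dies, it is 0.

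**Does the reading matter?** If VFD is imputed directly, neither limit enters the listed model. If the components are imputed, both are still missing for these two children: 28-day ventilation is incomplete and 28-day survival is unknown. Ventilated time to date is not a listed variable, so the limits are unused on either reading.

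**Inputs for size.**

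- Pilot control ventilation (protocol Table 1): mean 97.8 h, CI 61.5 to 134.1.
- SD, assuming about 66 control children: (134.1 − 61.5) / 2 / 1.96 × √66 = 150 h.
- Lognormal shape (assumed): σ² = ln(1 + (150/97.8)²) = 1.21; median = 97.8 × exp(−1.21/2) = 53 h.
- Mortality 3.5% (assumed), within the 2-5% in protocol section 2.1.
- Withdrawal uniform over days 1 to 27, data use permitted (assumed).

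**Impossible draws.** About 89% of withdrawn children are already off the ventilator. Among the other 11%, about 66% of draws from the observed values exceed the largest VFD still possible. By day last seen ventilated, with mortality 2-5%:

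| Day | Limit | Share of draws above it |
|---|---|---|
| 3 | 25 | 58-59% |
| 7 | 21 | 81-83% |
| 14 | 14 | 90-93% |

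**How many children.** If 10% of 1,320 records were affected: 132 × 0.11 ≈ 15 children still ventilated. If 2% were: 26 × 0.11 ≈ 3.

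**Precision.** Simulated trials of 660 per arm compared the listed model with one that keeps the observed part. The variance of the treatment difference, mean or median, rose by about 2-3%, 5-7% and 13% with 2%, 5% and 10% of records affected. A simpler run for the median, without age strata, gave 1%, 6% and 10%. For the confidence interval, √1.03 = 1.015 and √1.13 = 1.063, so it is roughly 1.5% to 6% wider. The ratios depend on how well the alternative model uses the observed part.

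**The case against.** The strongest reply is that the rule is terse and not necessarily wrong. Fully conditional specification suggests that components are imputed in turn, which would keep any component that is complete. The analysis code is said to be on GitHub, which I could not see, and it may bound the draws. Affected records may be few: withdrawn children contribute only if data use is permitted, 28-day status is collected, and primary-outcome items are verified for every enrolled child. Much of this stands, and it limits the size of the problem. It does not remove it, because the two children above have neither component complete and the SAP's list leaves out what is known about them.

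Some stronger readings are tempting but not supported:

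- *Known VFDs are overwritten.* A child whose VFD is fully determined does not trigger imputation. The fault is that partial information goes unused.
- *Children who died receive positive VFDs.* The trigger is a missing component that is required for the calculation. With death known, the zero rule in S2 leaves nothing else required, so the natural reading is VFD = 0. The order of steps is unstated and deserves a sentence.
- *The protocol's withdrawal section is contradicted.* It says earlier results are included in the analysis, and the missing-data section does not exclude them.
- *About 27-36% of draws would exceed 28 days.* This assumes a normal linear imputation step, with the SD implied by the sample-size text (66 h / 0.33 = 200 h, or 8.3 days) and means of 23-25 days. The SAP names no such step and treats VFD as non-normal.

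**Conclusion.** The point holds as a shortcoming of the imputation model for children with incomplete 28-day follow-up. As listed, the model can give values that the record excludes, and it spends precision the trial has already bought. On the stated assumptions, about two thirds of draws for children still ventilated at withdrawal are impossible. The variance cost runs from about 2-3% to about 13% as the affected share goes from 2% to 10%. The upper figure needs every withdrawal in the planning allowance to be a partial record with data use permitted, so the real cost is probably lower. The ventilation distribution, the timing of withdrawal and the affected share are assumptions. No bias in the treatment effect is shown. This is a worthwhile, inexpensive improvement and does not threaten the primary result.

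**What to change.** In the SAP section Treatment of missing data:

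1. State that a known death within 28 days gives VFD = 0 before any imputation. This is a clarification.
2. Keep ventilated time already observed and impute only the unobserved part, with VFD limited to between 0 and 28 minus observed ventilated time. Say whether VFD or its components are imputed.
3. Add ventilated time and intubation status at last observation to the imputation model and, optionally, the RACHS score.

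Predictive mean matching alone would keep values within 0 to 28 but would not enforce the child-specific limit, so step 2 is needed in any case.

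The cost is a few sentences and a few lines of code, using data already collected. The imputation model becomes slightly more complex. If the change comes after publication of the SAP, the SAP's own principles require that it be declared.

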#### **List of planned figures**

**Figure 1.** CONSORT participant flow diagram

**Figure 2.** Cumulative incidence functions for extubation (accounting for mortality) (all patients, and the pre-specified subgroups)

**Figure 3.** Composite figure of a) bar chart depicting proportion of patients with LCOS, b) mean (and 95% CI) SaO2-ScvO2 difference, c) boxplot of lactate levels, d) boxplot of VIS score, e) mean (and 95% CI) of creatinine values, over time points 0, 6, 12, 24, 48 hours after PICU admission, f) PELOD-2 score at 0, 24, 48 hours after PICU admission, separated by treatment group

#### **List of planned supplementary material**

- Funding sources
- Trial committee and NITRIC trial investigators
- Data and Safety Monitoring Board Terms of Reference
- Data and Auditing Monitoring Plan
- Enrolment statistics by site and country
- List of congenital heart disease conditions and surgeries
- List of protocol violations
- Results of interim analyses
- Consent details
- Volume of blood product transfused between study arms
- Listing of adverse events
- Kaplan-Meier survival curves for length of PICU stay and length of hospital stay
- Results of subgroup analyses
- Forest plot of the treatment effect across subgroups for the primary and secondary outcomes.
- Results of sensitivity analyses

363 23. Gaies MG, Gurney JG, Yen AH, Napoli ML, Gajarski RJ, Ohye RG, et al.  
364 Vasoactive-inotropic score as a predictor of morbidity and mortality in infants after  
365 cardiopulmonary bypass. Pediatr Crit Care Med. 2010;11(2):234-8.

- 366 24. Leteurtre S, Duhamel A, Salleron J, Grandbastien B, Lacroix J, Leclerc F, et al.  
367 PELOD-2: an update of the PEdiatric logistic organ dysfunction score. Crit Care Med.  
368 2013;41(7):1761-73.
- 369 25. Kaddourah A, Basu RK, Bagshaw SM, Goldstein SL. Epidemiology of Acute Kidney  
370 Injury in Critically Ill Children and Young Adults. N Engl J Med. 2017;376(1):11-20.  
371  
372

Figure 1. Draft CONSORT participant flow diagram

[figure not shown]

377 Table 1. Baseline characteristics of infants enrolled in NITRIC trial  
378

| Characteristic                                                     | Standard Care
N= | Nitric Oxide
N= |
|--------------------------------------------------------------------|---------------------|--------------------|
| Age at randomisation (weeks)* median (IQR)                  |                     |                    |
| < 6 weeks n (%)                                             |                     |                    |
| ≥ 6 weeks n (%)                                             |                     |                    |
| Weight (kg) median (IQR)                                    |                     |                    |
| Female sex n (%)                                     |                     |                    |
| Ethnicity                                                   |                     |                    |
| Caucasian n (%)                                             |                     |                    |
| Aboriginal/Torres Strait Islander n (%)                     |                     |                    |
| Asian n (%)                                                 |                     |                    |
| Maori/Pacific Islander n (%)                                |                     |                    |
| Mixed/Other n (%)                                           |                     |                    |
| Congenital heart disease                                    |                     |                    |
| Univentricular* n (%)                                       |                     |                    |
| Biventricular* n (%)                                        |                     |                    |
| History of previous cardiac surgery on CPB n (%)            |                     |                    |
| Right-sided obstructive lesions n (%)                       |                     |                    |
| Tetralogy of Fallot n (%)                                   |                     |                    |
| Double outlet right ventricle (DORV) n (%)                  |                     |                    |
| Pulmonary stenosis/atresia n (%)                            |                     |                    |
| Tricuspid stenosis/atresia n (%)                            |                     |                    |
| Other n (%)                                                 |                     |                    |
| Left-sided obstructive lesions n (%)                        |                     |                    |
| Coarctation n (%)                                           |                     |                    |
| Interrupted aortic arch n (%)                               |                     |                    |
| Hypoplastic aortic arch n (%)                               |                     |                    |
| HLHS n (%)                                                  |                     |                    |
| Other n (%)                                                 |                     |                    |
| Shunt lesions n (%)                                         |                     |                    |
| ASD n (%)                                                   |                     |                    |
| VSD n (%)                                                   |                     |                    |
| AVSD n (%)                                                  |                     |                    |
| Truncus n (%)                                               |                     |                    |
| TGA n (%)                                                   |                     |                    |
| Persistent ductus arteriosus n (%)                          |                     |                    |
| Other n (%)                                                 |                     |                    |
| Various lesions n (%)                                       |                     |                    |
| Double-inlet left ventricle (DILV) n (%)                    |                     |                    |
| TAPVD n (%)                                                 |                     |                    |
| Other n (%)                                                 |                     |                    |
| Current ICU admission and treatments prior to heart surgery |                     |                    |

| Characteristic                                       | Standard Care
N= | Nitric Oxide
N= |
|-------------------------------------------------------------|-----------------------------|----------------------------|
| Intensive care admission n (%)                       |                             |                            |
| Duration of ICU stay (days) median (IQR)             |                             |                            |
| Treatments                                                  |                             |                            |
| Invasive ventilation n (%)                           |                             |                            |
| Duration of invasive ventilation (days) median (IQR) |                             |                            |
| Tracheostomy n (%)                                   |                             |                            |
| Inotropes n (%)                                      |                             |                            |
| Prostaglandin n (%)                                  |                             |                            |
| Steroids n (%)                                       |                             |                            |
| Afterload reducing agents n (%)                      |                             |                            |
| Inhaled nitric oxide n (%)                           |                             |                            |
| Sildenafil n (%)                                     |                             |                            |
| Comorbidities                                        |                             |                            |
| POPC                                                        |                             |                            |
| Good/normal n (%)                                    |                             |                            |
| Functionally normal n (%)                            |                             |                            |
| Mild overall disability n (%)                        |                             |                            |
| Moderate overall disability n (%)                    |                             |                            |
| Severe overall disability n (%)                      |                             |                            |
| Coma/vegetative state n (%)                          |                             |                            |
| Brain death n (%)                                    |                             |                            |
| Unknown n (%)                                        |                             |                            |
| Congenital syndrome n (%)                            |                             |                            |
| Trisomy 21 n (%)                                     |                             |                            |
| 22q11 n (%)                                          |                             |                            |
| Turner n (%)                                         |                             |                            |
| Noonan n (%)                                         |                             |                            |
| VACTERL n (%)                                        |                             |                            |
| CHARGE n (%)                                         |                             |                            |
| Other syndrome n (%)                                 |                             |                            |
| Country of hospital                                  |                             |                            |
| Australia n (%)                                      |                             |                            |
| New Zealand n (%)                                    |                             |                            |
| Netherlands n (%)                                    |                             |                            |
| Surgical complexity                                  |                             |                            |
| RACHS score median (IQR)                             |                             |                            |
| RACHS-1 n (%)                                        |                             |                            |
| RACHS-2 n (%)                                        |                             |                            |
| RACHS-3 n (%)                                        |                             |                            |
| RACHS-4 n (%)                                        |                             |                            |
| RACHS-5 n (%)                                        |                             |                            |
| RACHS-6 n (%)                                        |                             |                            |

| Characteristic                                                   | Standard Care
N= | Nitric Oxide
N= |
|------------------------------------------------------------------|---------------------|--------------------|
| Surgical procedure                                        |                     |                    |
| Tetralogy repair n (%)                                    |                     |                    |
| Norwood procedure n (%)                                   |                     |                    |
| Bicavopulmonary shunt n (%)                               |                     |                    |
| Right ventricular to pulmonary artery shunt/conduit n (%) |                     |                    |
| Fontan completion n (%)                                   |                     |                    |
| Arterial switch operation n (%)                           |                     |                    |
| ASD repair n (%)                                          |                     |                    |
| VSD repair n (%)                                          |                     |                    |
| AVSD repair n (%)                                         |                     |                    |
| Aortic arch repair n (%)                                  |                     |                    |
| Coarctation repair n (%)                                  |                     |                    |
| Truncus repair n (%)                                      |                     |                    |
| Pulmonary artery band n (%)                               |                     |                    |
| Ross procedure n (%)                                      |                     |                    |
| Left ventricular outflow tract surgery n (%)              |                     |                    |
| Right ventricular outflow tract surgery n (%)             |                     |                    |
| Valve surgery n (%)                                       |                     |                    |
| Valve repair n (%)                                        |                     |                    |
| Anomalous pulmonary vein repair n (%)                     |                     |                    |
| Heart Transplant n (%)                                    |                     |                    |
| Other n (%)                                               |                     |                    |

379 \*used for stratification  
 380 SD standard deviation; IQR interquartile range; POPC Pediatric Overall Performance  
 381 Category; CPB cardiopulmonary bypass; HLHS hypoplastic left heart syndrome; ASD atrial  
 382 septal defect; VSD ventricular septal defect; AVSD atrioventricular septal defect; TGA  
 383 transposition of the great arteries; TAPVD total anomalous pulmonary venous drainage; ICU  
 384 intensive care unit; VACTERL vertebral defects, anal atresia, cardiac defects, tracheo-  
 385 esophageal fistula, renal anomalies, and limb abnormalities; CHARGE coloboma, heart  
 386 defects, atresia choanae (also known as choanal atresia), growth retardation, genital  
 387 abnormalities, and ear abnormalities; RACHS risk adjustment for congenital heart surgery

388 Table 2. Surgical and perioperative characteristics of infants enrolled in NITRIC trial  
389

| Characteristic                                                | Nitric Oxide
N= | Standard Care
N= | Difference (95% CI) |
|---------------------------------------------------------------|--------------------|---------------------|---------------------|
| Cardiopulmonary bypass characteristics                 |                    |                     |                     |
| Blood prime n (%)                                      |                    |                     |                     |
| CPB duration (min) median (IQR)                        |                    |                     |                     |
| CPB <60minutes n (%)                                   |                    |                     |                     |
| CPB ≥60minutes n (%)                                   |                    |                     |                     |
| Cross-clamp n (%)                                      |                    |                     |                     |
| Cross-clamp (min) median (IQR)                         |                    |                     |                     |
| Number of CPB runs                                            |                    |                     |                     |
| 1 n (%)                                                |                    |                     |                     |
| 2 n (%)                                                |                    |                     |                     |
| 3 n (%)                                                |                    |                     |                     |
| ≥4 n (%)                                               |                    |                     |                     |
| Deep hypothermic arrest n (%)                          |                    |                     |                     |
| Duration of deep hypothermic arrest (min) median (IQR) |                    |                     |                     |
| Antegrade cerebral perfusion n (%)                     |                    |                     |                     |
| Modified ultrafiltration used n (%)                    |                    |                     |                     |
| Slow continuous ultrafiltration used n (%)             |                    |                     |                     |
| Blood products received in theatre                     |                    |                     |                     |
| Red blood cells (mL/kg) median (IQR)                   |                    |                     |                     |
| Whole blood (mL/kg) median (IQR)                       |                    |                     |                     |
| Platelets (mL/kg) median (IQR)                         |                    |                     |                     |
| Fresh frozen plasma (mL/kg) median (IQR)               |                    |                     |                     |
| Cryoprecipitate (mL/kg) median (IQR)                   |                    |                     |                     |
| Drug treatments received in theatre                    |                    |                     |                     |
| Intravenous steroids n (%)                             |                    |                     |                     |

|                                                                                                          |  |  |  |
|----------------------------------------------------------------------------------------------------------|--|--|--|
| Inhaled NO n (%)                                                                                  |  |  |  |
| Administration of study drug (nitric oxide)                                                       |  |  |  |
| Time from start of CPB to start of NO (min) mean (SD)/median (IQR)                                |  |  |  |
| Duration of NO on CPB (min) median (IQR)                                                          |  |  |  |
| Proportion of time spent on CPB with NO* mean (SD)/median (IQR)                                   |  |  |  |
| Change in methaemoglobin level (%) between start and post-CPB mean (SD)/median (IQR) ^ |  |  |  |
| Change in methaemoglobin level (%) between start and post-CPB >3% ^ n (%)              |  |  |  |

390     \* if multiple CPB runs during the same surgery, summarising every CPB run individually; ^ calculated as post-CPB methaemoglobin – pre-CPB

391     methaemoglobin

392     IQR interquartile range; CPB cardiopulmonary bypass; SD standard deviation; NO nitric oxide

393 Table 3. Primary and secondary outcomes per intention-to-treat analysis

394

| Outcome                                                               | Standard Care
N= | Nitric
Oxide
N= | Unadjusted
p-value | Estimate of
Difference
(95% CI) | Adjusted
p-value |
|-----------------------------------------------------------------------|---------------------|-----------------------|-----------------------|---------------------------------------|---------------------|
| Primary Outcome                                                |                     |                       |                       |                                       |                     |
| Ventilator-free days median (IQR)                              |                     |                       |                       |                                       |                     |
| Secondary Outcomes                                             |                     |                       |                       |                                       |                     |
| Duration of invasive ventilation median (IQR)                  |                     |                       |                       |                                       |                     |
| Low cardiac output syndrome, need for ECLS or death n (%)      |                     |                       |                       |                                       |                     |
| Low cardiac output syndrome n (%)                              |                     |                       |                       |                                       |                     |
| ECLS n (%)                                                     |                     |                       |                       |                                       |                     |
| Death n (%)                                                    |                     |                       |                       |                                       |                     |
| Length of stay in PICU median (IQR)                            |                     |                       |                       |                                       |                     |
| Length of stay in hospital median (IQR)                        |                     |                       |                       |                                       |                     |
